### Intervention

2.8

The intervention protocols are designed based on traditional Chinese medicine theory (TCM), clinical guidelines, and expert consensus. All acupuncturists must hold valid Chinese medical practitioner license and has completed specialized training. All participants will receive standard treatment for ischemic stroke, including blood pressure control, blood glucose control, lipid control, antiplatelet therapy, and other symptomatic and preventive treatments. Specific treatment recommendations are based on the guidelines outlined in the Chinese Guidelines for the Diagnosis and Treatment of Acute Ischemic Stroke (2023) (14) and the Chinese Guidelines for Secondary Prevention of Ischemic Stroke and Transient Ischemic Attack (2022) (18). Specific medications, dosages, and target goals are detailed in Table 1. Swallowing rehabilitation training will be applied three sessions per week under professional supervision for four consecutive weeks.

**TABLE 1 T1:** Standardized secondary prevention protocol for ischemic stroke.

Parameter	First-line drug and dose	Target value	Monitoring time-point	Non-adherence management
Blood pressure	Amlodipine 5 mg once daily or irbesartan 150 mg once daily; add the alternate agent if BP uncontrolled after 2 weeks	< 130/80 mmHg	Baseline, 2, 4, 8 weeks	If BP remains ≥ 140/90 mmHg at two consecutive visits, investigators will uptitrate the dose or initiate dual therapy; if target is still not achieved, the case will be recorded as a protocol deviation.
LDL-cholesterol	Atorvastatin 20 mg once nightly	< 1.8 mmol/L or a ≥ 50 % reduction from baseline	Baseline, 4, 8 weeks	If LDL-C remains ≥ mmol/L, add ezetimibe 10 mg once daily and review diet adherence
Glycaemic control	Metformin 0.5 g twice daily; step-wise insulin regimen if intolerance or HbA1c > 10 %	Fasting plasma glucose 4.4–7.0 mmol/L; HbA1c < 7 %	Weekly finger-stick; venous sample every 4 weeks	If two consecutive fasting glucose values exceed 10 mmol/L, investigators will initiate basal-bolus insulin.
Antiplatelet therapy	Aspirin 100 mg once daily; if aspirin-intolerant, clopidogrel 75 mg once daily	Patients will continue the assigned antiplatelet dose.	Baseline, every follow-up	Missed doses ≥ 3 consecutive days = non-adherence; counsel and re-educate; switch drug if adverse event
Swallowing basic care	Oral hygiene, thickened fluid, postural adjustment per Scottish Intercollegiate Guidelines; no ad libitum oral intake except study diet	Daily actual intake recorded	Daily by study nurse	Any unauthorized oral intake recorded as protocol deviation

#### The experimental group

2.8.1

Disposable sterile acupuncture needles (0.30 mm × 40 mm and 0.30 mm × 75 mm, Hwato brand, Suzhou Medical Supplies Factory Co., Ltd., China) will be used. The “Tong Guan Li Qiao” acupuncture therapy (19) will be administered according to TCM theory. The protocol includes the following bilateral acupoints: GB20 (Fengchi), GB12 (Wangu), TE17 (Yifeng), and CV23 (Lianquan) (Figure 2 and Table 2).

**FIGURE 2 F2:**
[figure not shown]
Location of acupuncture points (Source: Atlas of meridians and acupuncture points by JiuDaifu).

**TABLE 2 T2:** Anatomical location of selected acupoints.

Acupoints	Location
GB20 (Fengchi)	In the posterior region of the neck, under the occiput, in the depression between the upper part of the sternocleidomastoid muscle and the upper part of the trapezius muscle.
GB12 (Wangu)	On the neck, at the posterior and inferior depression of the mastoid process behind the ear.
TE17 (Yifeng)	On the neck, behind the earlobe, at the anterior and inferior depression of the mastoid process.
CV23 (Lianquan)	In the anterior region of the neck, on the anterior median line, above the laryngeal prominence, and in the depression of the upper edge of the hyoid bone.

Patients will lie in a supine position. GB20 (Fengchi) needles will be bilaterally inserted at a 30° inferior angle toward the thyroid cartilage to a depth of 2.5–3.0 cun (≈65–75 mm). Small-amplitude, high-frequency twisting manipulation will be applied for 1 min to achieve strong stimulation, targeting a throat numbness/swelling sensation called “deqi.” GB12 (Wangu) and TE17 (Yifeng) will be needled with the same depth, angle, and technique as GB20. CV23 (Lianquan) will be inserted to 1.0–1.5 cun (≈25–40 mm) with lifting-thrusting manipulation. All needles will be retained for 30 min. Participants will receive three sessions per week for four consecutive weeks.

Deqi will be assessed subjectively using the Chinese version of the Massachusetts General Hospital Acupuncture Sensation Scale (c-MASS) (20), which evaluates 12 distinct sensations to quantify deqi intensity and quality. Participants will self-complete the c-MASS within 30 s after each needle manipulation. In accordance with prior domestic research (21), “adequate deqi” will be defined as a total c-MASS score ≥ 4, accompanied by at least two typical sensations (soreness, numbness, fullness, or heaviness) each rated ≥ 3. Cases not fulfilling both criteria will be classified as “inadequate deqi.” The Deqi Quality Index (DQI) for each participant will be calculated as the mean of the total c-MASS scores recorded at three time points: initiation of intervention, 15 and 30 min.

During participant completion of the c-MASS, acupuncturists will simultaneously record their “hand sensation” using a visual analog scale (VAS). All acupuncturists will receive standardized training before the study begins, including consistent anchor definitions for the 0- and 10-point marks on the VAS, to minimize inter-practitioner scale drift. All deqi-related data will be documented in case report forms (CRF).

#### The rehabilitation control group

2.8.2

The rehabilitation control group will receive swallowing rehabilitation training three sessions per week under the guidance of professionals, with specific operations as follows:

##### Oral motor training

2.8.2.1

(1)   Patients perform active lip and tongue movement exercises under guidance.(2)   Tongue pressure resistance training: A biofeedback device is used to improve tongue pressure and mobility.(3)   Tongue muscle rehabilitation: Use a tongue muscle rehabilitation trainer (suction device) to apply passive traction or active-assistive movement and resistance training during tongue movement.(4)   Masako maneuver: The tongue is held in protrusion during swallowing to facilitate anterior movement of the pharyngeal wall, increasing pharyngeal pressure and accelerating the progression of the bolus.(5)   Shaker exercise: In supine position, patients elevate the head (shoulders remain on bed) to direct their gaze toward their toes. While holding the head at the highest point, they will maintain this position for 60s × 3 repetitions (with 60s rest intervals); then maintain a steady pace to raise the head and visualize toes 30 times.

##### Airway protection methods

2.8.2.2

(1)   Mendelsohn maneuver: Patients are trained to voluntarily prolong laryngeal elevation and maintain elevation for ≥ 1.5 s per swallow.(2)   Supraglottic Swallowing: Patients are trained to close the glottis before swallowing initiation to prevent aspiration of food or liquids, and to cough immediately after swallowing to clear any remaining food from the vocal cords.(3)   Effortful swallow: Patients are trained to perform multiple forceful swallows during the pharyngeal phase of swallowing.

#### The healthy control group

2.8.3

At baseline, functional MRI will be conducted to assess Regional Homogeneity (ReHo) and Amplitude of Low-Frequency Fluctuations (ALFF), together with Fiberoptic Endoscopic Evaluation of Swallowing (FEES). The study will not involve additional interventions or follow-up assessments, as published evidence (22, 23) supports the 12-month stability (ICC ≥ 0.75) of these resting-state and swallowing-related fMRI metrics. Further MRI scans would entail unnecessary radiofrequency exposure and patient travel burden, offering no clinical benefit and contravening the minimal-risk ethical principle.

### Outcome measures

2.9

#### Primary outcomes

2.9.1

The Functional Oral Intake Scale (FOIS) is a validated 7-point ordinal scale that assesses functional feeding status, ranging from tube feeding dependence (level 1) to unrestricted oral intake (level 7) (24). It will be used to assess the functional oral intake of PSD patients and as a eligibility criterion for selecting participants. Existing evidence indicates that acupuncture typically improves FOIS scores by 1–2 points (25), though treatment response varies with baseline characteristics, specific acupuncture parameters and intervention duration. For patients with initial scores of 2–4, achieving normal swallowing levels (FOIS ≥ 6) after 4 weeks of acupuncture treatment will be considered indicative of treatment effectiveness (26). The FOIS has been well-established as a reliable outcome measure for tracking longitudinal changes in swallowing function among stroke patients (27). Its standardized design and clinical relevance have led to widespread adoption in dysphagia research.

#### Secondary outcomes

2.9.2

##### Recovery of the swallowing center and peripheral nerves

2.9.2.1

(1) fMRI data acquisition and analysis

Functional magnetic resonance imaging (fMRI) will be acquired to measure ReHo and ALFF indicators, which will be assessed before and during treatment. The ReHo indicator quantifies local neural activity synchronization, with changes indicating functional reorganization at the regional level (28). The ALFF metric reflects spontaneous neural activity intensity, thereby indicating the dynamic changes in brain functional reorganization (29).

Structural images are obtained using a TI-3D MPRAGE sequence with a sagittal scan orientation (left-to-right acquisition), yielding high-resolution T1-weighted images of the whole brain. Scan parameters are: repetition time (TR)/echo time (TE) = 2,000 ms/1.97 ms; flip angle (FA) = 8°; number of excitations (NEX) = 0.5; field of view (FOV) = 256 × 256 mm; matrix size = 256 × 256; slice thickness = 1.0 mm; no gap; 192 slices; scan time = 4 min 40 s; total images = 190.

Resting-state fMRI (rs-fMRI) data are acquired using a gradient-echo (GRE) single-shot echo-planar imaging (EPI) sequence. Scan parameters are: TR/TE = 2,000 ms/30 ms; FA = 90°; FOV = 220 × 220 mm; matrix = 64 × 64; slice thickness = 3 mm; gap = 3 mm; 37 slices; 240 time points; scan time = 8 min 8 s; producing 2,037 volumes.

Functional MRI data will undergo a standardized preprocessing pipeline. First, DICOM images will be converted to NIfTI format, followed by the exclusion of participants exhibiting excessive head motion—defined as translation exceeding 2 mm or rotation > 2°—or signal artifacts. Subsequent core preprocessing will include realignment for motion correction, slice timing adjustment, spatial normalization to the MNI152 template at 2 mm^3^ isotropic resolution, nuisance regression incorporating six head motion parameters along with cerebrospinal fluid and white matter signals, and band-pass filtering between 0.01 and 0.08 Hz. Finally, spatial smoothing will be applied using a 6 mm full-width-at-half-maximum Gaussian kernel.

Regions of interest (ROIs) will be defined based on the Automated Anatomical Labeling (AAL) atlas (30). In accordance with previous neuroimaging studies on swallowing mechanisms (31), the ROIs will include the precentral gyrus, insula, and anterior cingulate cortex.

(2) Surface electromyography (sEMG) detection

Surface electromyography (sEMG) testing is used to assess the coordination of local swallowing muscle groups, with evaluations conducted before, during, and after treatment. The tested muscle groups include the upper and lower oral sphincter muscles, masticatory muscles, submental muscle groups (comprising the anterior belly of the digastric muscle, mylohyoid muscle, and geniohyoid muscle), and subhyoid muscle groups (including the thyrohyoid muscle and sternohyoid muscle). The electrode placement locations are illustrated in Figure 3. Primary analysis indicators consist of swallowing action duration (seconds), amplitude of electromyographic activity (mean value), waveform patterns, and swallow count during continuous swallowing testing (32).

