#### Functional imaging evaluation indicators

2.12.1

Statistical analysis is performed using the DPABI V5.1^3^ software package. Whole-Brain Analysis: Paired *t*-tests will be used to compare pre- and post-intervention ALFF, fALFF, ReHo, and FC values within each group (acupuncture and rehabilitation training), as well as between groups after intervention. Based on prior evidence indicating direction-specific neuromodulation by acupuncture in swallowing networks (47, 48), the resulting statistical maps will be corrected using one-tailed Gaussian random field theory (voxel *p* < 0.01, cluster *p* < 0.05). ROI Analysis: Mean ReHo and ALFF values will be extracted from each ROI and analyzed using repeated-measures ANOVA to assess within-group changes over time and between-group differences.

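### Head motion is controlled within each scan only; with no motion term at group level, residual movement could create or mask a change in the secondary ReHo/ALFF outcomes

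*Protocol article*

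**What the plan says.** Section 2.9.2.1 (1) of the protocol article sets out the preprocessing in order. It begins with "the exclusion of participants exhibiting excessive head motion", which is "defined as translation exceeding 2 mm or rotation > 2" degrees; signal artifacts are also a reason for exclusion. Then: "Subsequent core preprocessing will include realignment for motion correction, slice timing adjustment", normalization, "nuisance regression incorporating six head motion parameters along with cerebrospinal fluid and white matter signals", "band-pass filtering between 0.01 and 0.08 Hz", and 6 mm smoothing. The functional images have "FOV = 220 × 220 mm; matrix = 64 × 64".

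Section 2.12.1 gives the group analyses. For whole-brain maps, "Paired *t*-tests will be used to compare pre- and post-intervention ALFF, fALFF, ReHo, and FC values within each group", with a comparison between groups after the intervention and a one-tailed cluster correction. For regions of interest, "Mean ReHo and ALFF values will be extracted from each ROI and analyzed using repeated-measures ANOVA". Neither names a covariate.

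Section 2.12.5 lists confounders for the primary and secondary outcomes: age, sex, duration, baseline NIHSS and FOIS, stroke subtype, comorbidities, expectation and deqi. Head motion is not among them, though the list is worded as non-exhaustive. Section 2.11 refers to pre-specified DPABI settings without listing them all.

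**The concern.** ReHo measures how synchronous neighbouring voxels are, and ALFF measures how strongly the signal fluctuates. A movement disturbs many neighbouring voxels at once, so whatever survives preprocessing bears directly on both. A displacement cut-off catches gross motion but not repeated small movements. Six same-volume linear regressors cannot represent a signal disturbance that depends on the size of a movement regardless of its direction, or one that lasts into the next volume.

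This population makes the nuisance potentially informative. All patients enter with FOIS 2 to 4 and are scanned at baseline, day 15 and day 30. Coughing and throat discomfort are listed in 2.9.3.1 as possible treatment-related events. It is a reasonable inference, though not something the document states, that coughing, throat clearing or saliva swallowing in the scanner changes as patients recover. Motion would then be a post-randomisation variable linked to outcome, which randomisation does not balance.

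At stake is the mechanistic aim. Section 2.9.2.1 reads ReHo change as functional reorganisation, and 2.1 makes the neural mechanism an objective.

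**Working it through.** **The only sample-size figure in the plan.** It is for FOIS, not imaging, but it supplies the 40 per arm used below. With a difference of 1.31 − 0.31 = 1.00, a margin of 0.39, SD 1.09, one-sided 5% and 80% power:

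n = 2 × 1.09² × (1.645 + 0.842)² / (1.00 − 0.39)² ≈ 39.5, so 40 per arm; 40 / 0.8 = 50 per arm, 100 in total.

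This reproduces the plan. No power or motion figure is stated for fMRI.

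**What the cut-off lets through** (2.9.2.1):
- In-plane voxel: 220 / 64 = 3.44 mm.
- 2 mm as a share of a voxel: 2 / 3.44 = 58%.
- 2° of rotation at an assumed 50 mm radius: 50 × 2 × π / 180 = 1.75 mm.

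**What a residual motion effect could do.** All inputs here are assumptions. Let r be the correlation between change in motion and change in ReHo/ALFF (0.2 to 0.4). Let d be the motion difference in SD units (0.3 to 0.5): the difference between arms in motion change for the between-arm test, and the change within the arm for the pre/post test. The spurious shift is b = r × d, from 0.2 × 0.3 = 0.06 SD to 0.4 × 0.5 = 0.20 SD. With 40 per arm and no true effect, the non-centrality is b√(40/2) between arms (0.27 to 0.89) and b√40 within an arm (0.38 to 1.26). Rejection rates from the non-central t distribution for a single 5% test:

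| Test | Between arms | Within arm |
|---|---|---|
| Two-sided | 5.8% to 14.3% | 6.6% to 23.5% |
| One-sided, bias in the tested direction | 8.4% to 22.4% | 10.2% to 34.4% |
| One-sided, bias against it | 2.8% down to 0.6% | 2.2% down to 0.2% |

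These are single-test rates, not rates under the cluster correction in 2.12.1. The last row matters because the whole-brain maps are one-tailed.

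**Direction.** If movement raises ReHo and recovering patients move less, the artefact is a fall in ReHo. The Discussion reports that ReHo varies inversely with dysphagia severity, so recovery should raise it. On that reading the artefact masks the expected effect. If movement increases instead, for example through throat discomfort, it would imitate the effect. For ALFF the document gives no direction, and 2.12.1 does not name the tail.

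**Do the stated regressors remove it?** Simulations used 240 volumes, 27 voxels, brief 1 mm movements that the 2 mm rule allows, and shared artefacts of assumed size.
- Six motion parameters only: ReHo rose from 0.36 to between 0.37 and 0.52, depending on the size and form of the artefact. The between-run SD was about 0.04.
- Six parameters plus CSF and white-matter signals: 0.37 to 0.38 if those signals carry the artefact fully, 0.37 to 0.42 at half strength, and 0.38 to 0.51 in a less favourable construction.
- The 24-parameter set: back to about 0.36.

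The last result is favourable by construction, since an artefact that follows the size of a movement is close to what squared terms represent. It shows that the larger set can help, not how much it will help here.

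**The case against.** The strongest reply has four parts.

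First, the plan does more than apply a cut-off and six regressors. Realignment, artifact exclusion, tissue-signal regression and filtering are all specified. This stands: a reader might infer that motion is handled only by the cut-off and six parameters, and the text does not support that.

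Second, a reader might infer that less coughing would show up as a false benefit of acupuncture. The document does not support that either. The most natural mechanism lowers ReHo, opposite to the direction implied by the Discussion, and a between-arm bias also needs motion to change differently by arm. This stands, and the point is therefore one of bias in either direction.

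Third, every magnitude is assumed. This stands too. The rejection rates are illustrations and not estimates of this trial's error rate.

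Fourth, the article condenses a fuller plan, and a group-level motion covariate may sit in the DPABI settings or the analysis plan. This stands in part. A covariate may exist there, and the article's silence is not proof that it does not. But the article does not leave motion open: it fixes a specific nuisance model and names the group tests, and the comment is on those stated choices.

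**Conclusion.** The point holds as a low-cost improvement to the secondary imaging outcomes. As written, motion is controlled within scans, and no group-level check is named. Sub-threshold movement therefore remains a possible alternative explanation for a change in ReHo or ALFF, or for the absence of one. The within-arm pre/post tests are most exposed because they have no randomised comparison to protect them; the between-arm tests are exposed only if motion changes differently by arm.

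The size cannot be derived from the document. The assumed bias of 0.06 to 0.20 SD moves a nominal two-sided 5% rate to somewhere between 5.8% and 23.5%, and can push a one-sided rate below nominal if the bias runs against the tested direction. That movement changes with recovery is an inference. FOIS and its analysis are not affected.

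**What to change.** **In 2.9.2.1**, replace the six-parameter regression with the 24-parameter set (the six parameters, their values at the previous volume, and the squares of both). Keep the CSF and white-matter regressors.

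**In 2.12.1**, add the following:
- Compute mean framewise displacement for each scan from the existing realignment output and report it by arm and visit.
- Repeat the whole-brain and region-of-interest comparisons with it as a scan-level covariate. For pre/post comparisons this means adjusting the change in the metric for the change in displacement. For the regions of interest, a mixed model of the kind already foreseen in 2.12.5 can take a covariate that varies by visit.
- Present this as a sensitivity analysis beside the unadjusted result. Motion is measured after randomisation and may itself respond to treatment, so the adjusted estimate should not become the main between-arm result.

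**Cost.** No new scans and one extra table. The larger set uses 24 − 6 = 18 more regressors out of 240 time points (7.5%). Because the pass band leaves roughly 2 × 480 s × 0.07 Hz ≈ 67 degrees of freedom, the loss is somewhat more than nominal if the regressors are filtered too. If the DPABI settings or the analysis plan already include a group-level motion covariate, one sentence in 2.12.1 saying so would settle that part.

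### If the listed fMRI order (band-pass filter, then 6 mm smoothing) is followed for every metric, whole-brain fALFF becomes degenerate or nearly so and ReHo is inflated by the smoothing kernel

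*Protocol article*

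**What the plan says.** Section 2.9.2.1 opens the processing paragraph with "Functional MRI data will undergo a standardized preprocessing pipeline". It then gives a sequence: conversion and motion exclusion first; then realignment, slice timing, "spatial normalization to the MNI152 template at 2 mm^3^ isotropic resolution", nuisance regression, "and band-pass filtering between 0.01 and 0.08 Hz"; and last, "Finally, spatial smoothing will be applied using a 6 mm full-width-at-half-maximum Gaussian kernel". The type of filter is not given. No metric is exempted from any step.

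Section 2.12.1 describes whole-brain paired tests to "compare pre- and post-intervention ALFF, fALFF, ReHo, and FC values within each group". Its ROI analysis uses mean ReHo and ALFF only. The abstract, section 2.9.2.1 and Table 4 name ReHo and ALFF as the fMRI outcomes; fALFF appears only in the whole-brain list. Section 2.11 says that all fMRI data go through DPABI V5.1 under parameters fixed in advance, but does not list them.

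**The concern.** Two of the metrics depend on where in the sequence they are computed.

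fALFF is a ratio: amplitude in the low-frequency band over amplitude across the whole spectrum. A filter that has already removed everything outside the band makes numerator and denominator the same, or nearly so. The comparison then says little or nothing about the brain.

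ReHo measures how well a voxel's time course agrees with those of its neighbours. A Gaussian kernel mixes neighbouring time courses, so smoothing first creates part of the agreement that ReHo is meant to detect.

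ReHo matters more here. It is a named secondary outcome, measured at three visits and analysed both whole-brain and by ROI, and the Discussion reads changes in it as a possible sign of neural compensation. That reading is weaker if much of the value comes from the kernel.

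**Working it through.** The article states no fALFF or ReHo value, so there is no figure to reproduce. The check asks what the listed order does to each metric.

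**Inputs from section 2.9.2.1**
- "TR/TE = 2,000 ms/30 ms", so the highest resolvable frequency is 1/(2 × 2 s) = 0.25 Hz.
- "240 time points", so the series lasts 240 × 2 = 480 s and frequency bins are 1/480 = 0.00208 Hz apart: 120 non-zero bins, of which numbers 5 to 38 (34 bins) lie in 0.01-0.08 Hz.
- Kernel: sigma = 6/2.3548 = 2.55 mm, or 1.27 voxels at 2 mm.
- Native grid: 220/64 = 3.44 mm in plane; 3 mm slice plus 3 mm gap = 6 mm between slices.

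**Assumptions not in the article**
- fALFF = summed amplitude in 0.01-0.08 Hz divided by summed amplitude over all non-zero frequencies.
- ReHo = Kendall's W over a 27-voxel neighbourhood.
- Normalised voxels are 2 mm on each side.

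**fALFF (simulated series)**

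| Filter applied first | White noise, mean (SD) | 1/f noise, mean (SD) |
|---|---|---|
| None | 0.283 (0.021) | 0.399 (0.029) |
| Ideal | 1.000 (0.000) | 1.000 (0.000) |
| Butterworth, order 2 | 0.781 (0.038) | 0.834 (0.032) |
| Butterworth, order 4 | 0.839 (0.043) | 0.879 (0.035) |

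The unfiltered white-noise value agrees with the bin count: 34/120 = 0.283. With a roll-off filter, voxels still differ, but the denominator outside the band is only what the filter lets through.

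**ReHo in pure noise**
- Independent 2 mm voxels: 0.037 unsmoothed, which is 1/27. The band-pass filter alone leaves it at 0.037. With 6 mm smoothing it is about 0.56-0.57.
- Analytic check: smoothed white noise has correlation exp(-d²/(4 sigma²)) at distance d. Converting to rank correlation and averaging over the 27 × 27 pairs gives W = 0.566.
- Noise interpolated from the native grid to 2 mm: 0.35 unsmoothed and 0.66 smoothed in one simulation, about 0.38 and 0.70 in another. Smoothing therefore adds about 0.31-0.32, against 0.568 - 0.037 = 0.53 for independent voxels.

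**ReHo with a shared signal (independent 2 mm voxels)**

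| Share of variance | Unsmoothed | Smoothed first |
|---|---|---|
| 0.1 | 0.127 | 0.953 |
| 0.2 | 0.208 | 0.978 |
| 0.3 | 0.286 | 0.984 |
| 0.5 | 0.469 | 0.994 |

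ReHo still rises with true signal, but over a much narrower range near 1.

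**Does compression cost power?** Power depends on the standardised difference d, and the SD shrinks as well. Two groups of 60 simulated subjects were compared, with shared-signal share 0.25 against 0.35.
- Independent voxels: d = 2.57 unsmoothed and 2.18 smoothed; with a between-subject SD of 0.08 in the share, 1.15 and 1.08.
- Native-grid noise: 2.12 and 2.09; with that SD, 1.12 and 0.95.

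These are losses of about 1% to 15%. Repeating the comparison with new random numbers gave 2.80 and 2.26, 1.19 and 0.97, 2.04 and 2.12, and 0.94 and 1.04: from a loss of 19% to a gain of 11%. The model shows no large, consistent loss.

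**The case against.** The strongest reply is that no sentence says at which step a metric is computed. Section 2.9.2.1 describes preprocessing and section 2.12.1 describes tests; the link between them is inferred. Section 2.11 refers to parameters without listing them, so they cannot be assumed to equal those in section 2.9.2.1. A condensed article may also leave metric-level detail to a fuller document. This makes the finding conditional, but does not remove it. The article chose to give an order, with words of sequence and smoothing as the last step on the functional data, and exempts no metric. An analyst following the text would compute everything on filtered, smoothed data. This is a stated order, not an absent detail.

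Several stronger readings are tempting and are not supported:
- That fALFF must equal 1 in every voxel. This needs an ideal filter, and the filter type is not given.
- That ReHo measures mainly the kernel. Smoothed ReHo still rises with shared signal, and part of the noise floor comes from interpolation, whatever the smoothing order.
- That the ReHo comparisons lose much power, or are biased between arms. Neither is shown; the pipeline is the same for both arms and all visits.
- That ALFF fails too. It sums amplitude within the band that the filter passes, so it is not made degenerate.
- That a named outcome is empty. fALFF is listed only among the whole-brain tests.

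**Conclusion.** The point stands in conditional form: the order as written is wrong for fALFF and ReHo. Followed literally, it makes the whole-brain fALFF comparison empty (ideal filter) or nearly so (about 0.8 with a roll-off filter, against 0.28 unfiltered in white noise). It also lifts the pure-noise floor of ReHo to about 0.56 on independent 2 mm voxels, or to 0.66-0.70 on noise from the native grid, and pushes the scale towards 1.

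These sizes rest on simulated noise, the usual definitions of fALFF and ReHo, and 2 mm voxels. They describe the metrics, not the trial's power. What is at stake is the meaning of the ReHo results and of the fALFF maps. The primary FOIS outcome is not touched.

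**What to change.** In section 2.9.2.1, replace the single order with one per metric:
- compute fALFF, with ALFF in the same run, from data that have not been band-pass filtered;
- compute ReHo from filtered but unsmoothed data, and apply the 6 mm kernel to the resulting ReHo maps;
- take the ROI means in section 2.12.1 from metrics computed in the same order.

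The cost is one paragraph and reprocessing of existing data. No new scans are needed.
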